#### Imaging procedures

2.7.3

A standard NCCT and CTA are conducted when admitted in emergency department, by a 64-slice CT scanner (SOMATOM Definition Flash; Siemens Healthcare Sector, Forchheim, Germany). The scanning parameters of NCCT are 120 kVp, 340 mA, and 5 mm slice thickness. The hematoma volume is calculated by the ABC/2 method.^[30]^ CTA is initiated after the infusion of 100-mL contrast material (80 kVp, 110 mA, 1 mm slice thickness, and pitch 1:1). 3D reconstructions of CTA are performed to assess the level of cerebrovascular stenosis. NCCT (120 kVp, 340 mA, and 5 mm slice thickness) and CTP are conducted 24 ± 3 hours after randomization in order to assess for additional HE and perihaematoma rCBF with different treatments. The CTP will be initialed after the infusion of 42 mL contrast material given over 12 seconds with CT images acquired every 1.5 seconds at most 50 seconds (70 kVp, 150 mA, 1 mm slice thickness).

#### Primary outcomes

2.7.4

The relative reduction of the perihematoma rCBF is considered as the key primary outcome. Relative reduction of rCBF = 1-(rCBF / contralateral homologous regions rCBF).^[14]^ The other primary outcomes include absolute CBF, Tmax, mean transit time (MTT), and rCBV of perihematoma region, those indexes of global and hemisphere, the rate of ischemic stroke within 7 days, volumes of parenchymal hematoma, IVH, and ischemic region.

#### Image analysis: CTA and CT perfusion

2.7.5

The stenosis is defined as the reduction of an artery diameter ≥50%^[31–33]^ or occlusion with digital subtraction angiography (DSA), magnetic resonance angiography, or CTA, and severe is defined as ≥70%.^[34]^ The cut-off values on CTA should be 30% to detect all lesions ≥50% on DSA, by which the CTA has a similar high sensitivity and specificity for detecting the stenosis of large cerebral vessels.^[35]^ The stenosis is detected by 3D image of CTA, and then the level of stenosis is calculated by the 2D gray scale MPR images with window and level of 1000 and 500 HU (Fig. 2), respectively.^[36]^ AHA/American Stroke Association guidelines^[29]^ suggest that severe cerebrovascular stenosis is a contraindication for intensive treatment. The included patients are divided into groups according the location of stenosis, such as anterior circulation (internal carotid artery, anterior cerebral artery, middle cerebral artery, posterior cerebral artery) and posterior circulation (vertebral artery or basilar artery and others lesions). Raw contrast-enhanced CT images are analyzed by a technician and are checked by a senior technician to ensure the accuracy. The perhematoma region is defined as the region of 1 cm from the margin of hematoma, excluding subarachnoid and intraventricular space.^[37]^ The vessels are also removed from the region, which show as voxel with CBF >100 mL/100 g/min or 8 mL/100 g.^[38–40]^ The mean rCBF, Tmax, MTT, and rCBV of perhematoma region and contralateral homologous regions are calculated with removal of vessels. In addition, the mean rCBF, Tmax, MTT, and rCBV of hemisphere are also used to analyze the difference in 2 treatments. Hypoperfusion is defined as absolute CBF <18 mL/100 g/min, or delay of MTT and Tmax more than 2 seconds, and severe hypoperfusion is CBF <12 mL/100 g/min.^[41,42]^ Relative rCBF, Tmax, MTT, and rCBV are defined the ratio of parameters of perhematoma region to those of contralateral homologous regions (Fig. 2).

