### Study objective

2.2

The key primary objective is to compare the relative reduction of peri-hematoma rCBF in sICH patients with cerebrovascular stenosis under different BP treatments and discuss whether the degree of stenosis or location of stenosis on relative main arteries has an effect on the peri-hematoma rCBF by analysis of subgroups. The other primary objectives are to analyze the absolute change of cerebral perfusion indexes, the occurrence rate of ischemic stroke, and incidence of hematoma expansion within 7 days. The key second objective is to determine the effects of different BP managements on unfavorable clinical outcome at 90-day in sICH patients with cerebrovascular stenosis. The other secondary objectives are to assess the effects of the treatments separately on death and dependency through physical function, health-related quality of life, other vascular events, and hospital stays.

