### Randomization

2.5

Patients are assigned to intensive BP-lowering group and conservative BP-lowering group by a minimization random allocation system (minimpy 0.3). They are stratified by level of stenosis and location of stenosis. All information of patients is collected and randomization is stratified by a special researcher within 1 hour after admission in department of emergency. Once the group is determined, the allocation is not allowed to change unless quit from the trial.

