### Statistical analysis

2.9

The analysis of this study is based on the intention-to-treat principle. The continuous variable of primary outcome and second outcomes will be assessed by *t* test. The Chi-square test will be used to assess the categorical data of second outcomes. Log-rank test will be used to analyze the time-to-event type of outcomes. Subgroup analysis will be conducted by level of cerebrovascular stenosis and location of the cerebrovascular stenosis.

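### The location definition places the posterior cerebral artery in the anterior circulation, so the planned anterior/posterior subgroup mixes vascular territories

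*Protocol article*

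**What the plan says.** Section 2.7.5 (Image analysis) states: "The included patients are divided into groups according the location of stenosis". It then gives two classes. One is "anterior circulation (internal carotid artery, anterior cerebral artery, middle cerebral artery, posterior cerebral artery". The other is "posterior circulation (vertebral artery or basilar artery and others lesions". No reason is given for this grouping, and no other section defines location differently.

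Location is used or named in three further places:

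- Section 2.2 makes it part of the key primary objective: to "discuss whether the degree of stenosis or location of stenosis on relative main arteries has an effect on the peri-hematoma rCBF by analysis of subgroups".
- Section 2.9 plans it as one of two subgroup factors: "Subgroup analysis will be conducted by level of cerebrovascular stenosis and location of the cerebrovascular stenosis".
- Section 2.5 allocates patients "by a minimization random allocation system (minimpy 0.3") and says: "They are stratified by level of stenosis and location of stenosis". It does not list the levels of either factor.

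**The concern.** By standard anatomy the posterior cerebral artery is ordinarily the terminal branch of the basilar artery and belongs to the posterior circulation. The sentence in section 2.7.5 therefore assigns the basilar artery to one class and its usual branch to the other. An analyst who follows the text would count posterior cerebral artery stenoses as anterior.

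The posterior class also ends in an open category of other lesions. The wording does not settle whether this means other lesions of the posterior circulation or every lesion not named elsewhere.

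At stake is the answer to the location question within the key primary objective. If the effect of blood pressure lowering on peri-hematoma rCBF differs between territories, a mixed anterior class hides part of that difference, and the posterior class is left with fewer patients.

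**Working it through.** The protocol states no figure to reproduce here. The check is a comparison of sections, followed by simple algebra on the consequence.

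**Step 1: the classes as written against ordinary anatomy**

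| Vessel | Class in section 2.7.5 | Ordinary territory |
|---|---|---|
| Internal carotid, anterior cerebral, middle cerebral | Anterior | Anterior |
| Posterior cerebral | Anterior | Posterior (arises from the basilar) |
| Vertebral, basilar | Posterior | Posterior |
| Other lesions | Posterior | Not stated |

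One named vessel is misplaced and one category is undefined.

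**Step 2: where the classes are used**

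Sections 2.2 and 2.9 rely on location for the subgroup, and section 2.7.5 is the only definition available to them. Section 2.5 names location as a minimisation factor without giving levels. Use of the same two classes there is a reasonable inference, but it is not stated.

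**Step 3: effect on the subgroup contrast**

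Let A be the number of patients with truly anterior lesions, P the number with truly posterior lesions, and k the number within P whose lesion is in the posterior cerebral artery. Let d_A and d_P be the treatment effects in the two territories. Assume that posterior cerebral artery lesions respond like other posterior lesions, that patients are split evenly between arms within each territory, and that the posterior class is otherwise clean.

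- Labelled anterior effect = (1 − w)·d_A + w·d_P, with w = k/(A + k).
- Labelled posterior effect = d_P, estimated from P − k patients instead of P.
- Labelled contrast = d_P − [(1 − w)·d_A + w·d_P] = (1 − w)·(d_P − d_A).

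The contrast shrinks by the fraction w, and the posterior estimate loses k patients. If the open category also admits lesions that are not posterior, the posterior class is mixed as well and the contrast shrinks further.

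**Step 4: what can be said about size**

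The planned total is 80 (section 2.4). The documents give neither k nor P. If a share p of patients has a posterior cerebral artery lesion (assumption), then k = 80p:

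- p = 5%: 0.05 × 80 = 4 patients
- p = 10%: 0.10 × 80 = 8 patients
- p = 15%: 0.15 × 80 = 12 patients
- p = 20%: 0.20 × 80 = 16 patients

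To illustrate w, assume further that A = 64. Then k = 4 gives 4/68 = 6%, and k = 12 gives 12/76 = 16%.

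**Step 5: the overall comparison**

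Location is read from the admission CTA and classed by the same rule in both arms. A mislabelled baseline class cannot bias the overall comparison of the randomised groups, and the t test in section 2.9 does not use it.

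**The case against.** The strongest reply is that the misplacement is real but its reach is short. Four parts of that reply stand.

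- **Minimisation.** A reader might infer that the allocation itself used a wrong factor. Section 2.5 gives no levels, and section 2.7.5 introduces its two classes as examples within an image-analysis section. The link is plausible but unproven. Even if it holds, the cost is poorer balance on true territory, not bias.
- **Adjustment.** A reader might infer that covariate adjustment for location is weakened. Section 2.9 plans t, chi-square and log-rank tests and no such adjustment, so there is nothing there to weaken.
- **Other lesions.** A reader might infer that every unlisted lesion defaults to posterior. The phrase can equally mean other posterior-circulation lesions, in which case the class is only loosely described. The text is ambiguous, and no more than that can be claimed.
- **Size.** A reader might infer that a quarter to three quarters of the posterior group is lost, or that the subgroup cannot be interpreted at all. The first needs both a 5% to 15% share of posterior cerebral artery lesions and a posterior group of 16 (4/16 and 12/16), and the documents support neither figure. The second goes too far: under the same assumptions the contrast shrinks by 6% to 16%, and the rest of the cost is lost precision.

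It can also be said that section 2.4 powers only the overall comparison, so the subgroup is weak under any labelling. That limits the consequence, but it does not excuse a wrong definition of a factor that section 2.2 places in the key primary objective.

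**Conclusion.** The definition is wrong as written. It classes the posterior cerebral artery as anterior while classing the basilar artery, from which it ordinarily arises, as posterior, and it leaves the category of other lesions unclear. The location subgroup would mix territories, with a diluted contrast and a smaller posterior group.

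The number of patients affected cannot be calculated from the documents; it is 80p for an unknown share p. The direction of the dilution rests on posterior cerebral artery lesions behaving like other posterior lesions. The harm is confined to the location subgroup and, if minimisation uses the same classes, to balance on true territory. The main comparison is not biased.

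**What to change.** 1. In section 2.7.5, list the posterior cerebral artery with the vertebral and basilar arteries, or state and justify an exception, such as an artery that arises from the carotid.
2. State in the same sentence that the category of other lesions means only other lesions of the posterior circulation.
3. Run the location subgroup of section 2.9 on the corrected class, recoded from the stored baseline CTA.
4. Leave the location values already used for allocation unchanged in the randomisation record.

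The cost is a short amendment and some recoding of existing scans, with no new procedure for patients. One small drawback remains: for patients already randomised, the subgroup class may differ from the class used at allocation.

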### Secondary outcomes

2.8

The key secondary outcome is the clinical outcomes (death and disability) at 90-day. Disability is considered as modified Rankin score from 3 to 5 point. The other secondary outcomes include incidence of other vascular events, hospital stays, and health-related quality of life measured from the EQ-5D at 90 days.

### Statistical analysis

2.9

The analysis of this study is based on the intention-to-treat principle. The continuous variable of primary outcome and second outcomes will be assessed by *t* test. The Chi-square test will be used to assess the categorical data of second outcomes. Log-rank test will be used to analyze the time-to-event type of outcomes. Subgroup analysis will be conducted by level of cerebrovascular stenosis and location of the cerebrovascular stenosis.

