#### Exclusion criteria

2.3.2

(1)Known definite contraindication to intensive BP-lowering treatment (e.g., severe cerebrovascular stenosis (>70%), severe aortic valve stenosis, severe renal failure);(2)Known definite indication to intensive BP-lowering treatment (e.g., very high SBP ≥220 mm Hg; hypertensive encephalopathy; aortic dissection);(3)The ICH is caused by secondary factors (e.g., intracranial aneurysm; arteriovenous malformation; tumor stroke; anticoagulant correlation hemorrhage).(4)Glass coma scale ≤5 or deep coma;(5)Disabled or with underlying diseases (e.g., known dementia, severe cardiovascular disease, kidney failure) before onset;(6)History of ischemic stroke within 30 days before onset of sICH;(7)Known indication of emergency surgery (volume of supratentorial hematoma ≥30 mL or volume of infratentorial hematoma ≥10 mL; within 48 hours from onset; Glass coma scale ≥5);(8)Contraindication to CT perfusion imaging (CTP) (e.g., contrast allergy, pregnancy, or creatinine ≥160 mmol/L).

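### Parenchymal hematoma volume, listed as an other primary outcome, is assigned to an unadjusted t test although the admission CT already supplies the baseline volume; the test is valid but gives up precision.

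*Protocol article*

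**What the plan says.** All references are to the protocol article.

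- **Outcome.** Section 2.7.4 includes "volumes of parenchymal hematoma, IVH, and ischemic region" among the other primary outcomes. These are named as volumes. Neither a change from admission nor a time point is mentioned.
- **Test.** Section 2.9 says "The continuous variable of primary outcome and second outcomes will be assessed by" t test. No covariate is named.
- **Baseline scan.** Section 2.7.3 says "A standard NCCT and CTA are conducted when admitted in emergency department", and then "The hematoma volume is calculated by the ABC/2 method".
- **Follow-up scan.** The same section repeats the non-contrast CT at 24 ± 3 hours after randomization, "in order to assess for additional HE and perihaematoma rCBF with different treatments".
- **Allocation.** Section 2.5 uses minimization on level and location of stenosis only, so starting hematoma volume is not among the balanced factors.
- **Related objective.** Section 2.2 also names "incidence of hematoma expansion within 7 days" among the other primary objectives. Unlike the volume outcome, this is a binary measure.

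**The concern.** The 24-hour volume of a hematoma contains the blood that was there at admission. If the arms are compared on 24-hour volume alone, the spread of starting volumes enters the error term, although treatment cannot have affected it. The part that treatment can affect is growth after randomization.

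This matters because the Background says elevated blood pressure raises the risk of hematoma expansion. Hematoma volume is therefore a continuous measure of the possible benefit of intensive lowering, to be set against the perfusion outcomes that look for harm. In a trial of 80 patients sized only for rCBF, lost precision on volume makes an uninformative null result more likely.

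**Working it through.** **Inputs from the protocol.** Two-sided 5% level; 36 evaluable and 40 randomized per group (section 2.4). The protocol gives no power calculation for volume, so there is no figure of its own to reproduce on this point.

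**Assumptions.** The protocol gives no SD for volume, no SD for growth, and no correlation rho between admission and 24-hour volume. Each is varied below.

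**Step 1: variance removed by adjustment.** With a linear baseline covariate, the residual variance of the 24-hour volume is (1 − rho²) times its raw variance. The reduction is therefore rho²: 9% at rho 0.3, 25% at 0.5, 49% at 0.7 and 64% at 0.8.

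**Step 2: what this means for power.** Find the standardized difference d that the t test detects with a given power (non-central t). Divide it by √(1 − rho²) and recompute power with one fewer degree of freedom.

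- 80% power under the t test: d = 0.670 at 36 per group, 0.634 at 40.
- 50% power under the t test: d = 0.468 at 36 per group, 0.444 at 40.

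Example at 36 per group and rho 0.5: 0.670/√0.75 = 0.773, which gives 89.9% power.

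| Assumed rho | Adjusted power, from 80% | Adjusted power, from 50% |
|---|---|---|
| 0.3 | 84% | 54% |
| 0.5 | 90% | 62% |
| 0.7 | 97.5% | 78% |
| 0.8 | 99.7% | 90% |

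To the precision shown, the table is the same for 36 and 40 per group.

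**Step 3: which rho is plausible.** Write 24-hour volume as admission volume plus growth, with growth independent of admission volume. Then rho = SD_baseline / √(SD_baseline² + SD_growth²). Assume a baseline SD of 5 to 8.7 mL; the upper value is a uniform spread over 0 to 30 mL, 30/√12 = 8.66. Assume a growth SD of 2 to 6 mL.

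- Lowest rho, SDs 5 and 6: 5/√(25 + 36) = 0.64.
- Highest rho, SDs 8.66 and 2: 8.66/√(75 + 4) = 0.97.

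For an assumed 2 mL effect on growth at 36 per group, the normal approximation gives:

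| Baseline SD, growth SD (mL) | t test on volume | Baseline-adjusted |
|---|---|---|
| 5, 6 (lowest rho) | 19% | 29% |
| 7, 4 (middle) | 18% | 56% |
| 8.66, 2 (highest rho) | 16% | 99% |

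Adjustment has the higher power in all nine SD combinations examined, but the gain varies widely.

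**Step 4: chance imbalance at baseline.** With 40 per group, the 95% range of the difference in mean admission volume is ±1.96 × SD × √(2/40). This is ±2.2 mL for SD 5 and ±3.8 mL for SD 8.66. Under the additive model of step 3, an unadjusted comparison carries this into the treatment estimate. It is random error, and the t test's confidence interval already allows for it.

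**Step 5: validity.** Trials were simulated with admission volume uniform over 1 to 30 mL, growth SD 4 mL and 36 per group. With no treatment effect, the rejection rate was about 5% for the t test on volume, the t test on change, and ANCOVA. With a 2 mL effect, power was 14%, 54% and 54%.

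**The case against.** **The t test is valid under randomization.** This stands. A reader might infer that baseline differences bias the comparison or swamp the treatment effect. The documents do not support that. The error rate stays at about 5%, and how far starting volume dominates depends on SDs and a correlation that the protocol does not give. The harm is lost precision.

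**The benefit question is already answered against baseline.** Hematoma expansion is judged against the admission scan, so volume is not the only measure of growth. That also stands, but expansion is a separate binary incidence. It does not replace the volume comparison or make it more precise.

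**A change score may be intended.** Section 2.7.4 is a condensed list, and a t test on change from admission would fit the wording of section 2.9. In the step 5 simulation it performed as well as ANCOVA. If change is meant, most of the loss disappears, but the text says volumes and would need to say so. With equal variances, the change score has 2(1 − rho) times the raw variance, so it beats the raw volume only when rho exceeds 0.5. ANCOVA does not have that limit.

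**Covariates belong in an analysis plan.** Often they do. Here the article states the test for these outcomes, so the point concerns a stated choice and not a missing detail.

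**The size is assumed.** This stands. At rho 0.3 the gain is only about 4 points.

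**IVH is different.** This stands. ABC/2 is stated for hematoma volume only, no IVH method is given, and many patients may have no IVH. A reader might extend the same linear model to IVH volume, but the documents do not support that without conditions.

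**The trial does not rest on volume.** This is correct: the sample size and the key primary outcome concern rCBF.

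**Conclusion.** The point holds as an efficiency loss in a stated analysis. Parenchymal hematoma volume is labelled a primary outcome, its baseline value is already collected, and section 2.9 assigns it to a test that does not use that value. Over an assumed rho of 0.3 to 0.8, an effect with 80% power under the t test would have about 84% to 99.7% with adjustment. Under the additive growth model and the SDs assumed above, rho would be 0.64 or more, but none of those figures comes from the protocol.

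The conclusion rests on reading the outcome as volume and not change, and on a roughly linear relation with admission volume on the scale chosen. It does not extend to relative rCBF: section 2.7.3 has perfusion imaging only at 24 ± 3 hours, so there is no baseline to adjust for. The change is worth making because it costs almost nothing, but it does not threaten the validity of the trial.

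**What to change.** In section 2.9, exempt parenchymal hematoma volume from the general t test sentence and state:

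- 24-hour parenchymal hematoma volume is analysed by ANCOVA on treatment arm and admission-CT hematoma volume, on a log or other suitable scale if skewed.
- The adjusted mean difference is reported with its 95% CI.
- The unadjusted t test is kept as a sensitivity analysis.

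In section 2.7.4, name the time point and say that the outcome is the volume at that time.

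Treat IVH volume in the same way only if it is measured by the same method on both scans, and use a model that allows for patients with zero IVH.

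The cost is a sentence or two of wording, one degree of freedom, and an assumed form for the relation with baseline. No extra scans or patients are needed, because the admission scan and its ABC/2 volume are already part of the protocol.

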### Sample size

2.4

The initial assessment of sample size is based on taking peri-hematoma rCBF as the ischemic reign of brain tissue.^[14]^ For no study now available referring to the field, the pilot trial was conducted to assess the sample size.

The pilot data includes 12 patients (6/each group) and shows the rate of reduction of peri-hematoma rCBF are (0.4282 ± 0.14705) and (0.3555 ± 0.12592) in intensive/conservative BP-lowering group, compared with that of contralateral homologous reign. For the reduction of relative rCBF, ≥44%^[28]^ is regarded as a threshold of infarction, if the difference of 2 groups is more than 9% (9%+35.5%>44%); acute SBP lowering is considered to significantly increase the risk of infarction in these patients. So, each sample size of 36 in a group will be required to detect a significant difference of 5% (2-tailed) and a power of 90% (PASS software Version 11.0.4; NCSS). In view of 10% patients lost to follow-up, a total of 80 patients (40 in each group) will be included in this trial.

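### The t test for the key primary outcome leaves out the two minimisation factors, so it is conservative and loses power if those factors are prognostic

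*Protocol article*

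**What the plan says.** All of this is in the protocol article.

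- **Randomization (2.5).** Patients are allocated "by a minimization random allocation system (minimpy 0.3"), and "They are stratified by level of stenosis and location of stenosis".
- **Primary outcomes (2.7.4).** "The relative reduction of the perihematoma rCBF is considered as the key primary outcome". It is a continuous measure, one minus the ratio of peri-hematoma rCBF to that of the matching contralateral region.
- **Statistical analysis (2.9).** "The continuous variable of primary outcome and second outcomes will be assessed by" a *t* test. No adjusted or stratified form of the main comparison is stated. The two factors come back only here: "Subgroup analysis will be conducted by level of cerebrovascular stenosis and location of the cerebrovascular stenosis".
- **Study objective (2.2).** The key primary objective includes finding out "whether the degree of stenosis or location of stenosis on relative main arteries has an effect on the peri-hematoma rCBF". The article therefore treats the prognostic value of the two factors as a question to be answered, and gives no size for it.

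**The concern.** The analysis should reflect the way patients were allocated. Minimisation makes the arms alike on level and location of stenosis, so chance imbalance on those factors no longer adds to the sampling variation of the treatment difference. An unadjusted t test takes its standard error from the whole within-arm spread, including the spread due to the factors. If the factors predict the outcome, that standard error is too large, the confidence interval is too wide, and the real type I error falls below the nominal 5%.

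The cost is power. The trial asks whether intensive lowering worsens perfusion around the hematoma, so lost power makes a real loss of perfusion easier to miss. The article names the test for its key primary outcome, so this is a stated choice rather than a detail left open.

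**Working it through.** **Inputs from the Sample size section (2.4).** The pilot gives "0.4282 ± 0.14705) and (0.3555 ± 0.12592) in intensive/conservative BP-lowering group". The difference to detect is 0.09 ("if the difference of 2 groups is more than 9% (9%+35.5%>44"%). The test is two-sided at 5%, with 36 analysed per group.

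**Input not in the article.** R² is the share of outcome variance explained by level and location of stenosis together. It is an assumption, taken over the range 0 to 0.3.

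**Step 1: common SD and standard error.**
SD = √[(0.14705² + 0.12592²)/2] = 0.1369.
SE of the difference = 0.1369 × √(2/36) = 0.0323.

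**Step 2: the plan's own figure.**
n per group = 2 × (1.960 + 1.282)² × 0.1369² / 0.09² = 48.6, so 49 (50 with the t distribution). The stated 36 does not reproduce at 90% power. With 36 per group the t test has 78.5% power. That is a separate sample-size matter; here 78.5% is only the starting point, at R² = 0.

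**Step 3: what the t test does under balance.** With perfect balance on the factors, the true standard error of the difference is 0.0323 × √(1 − R²), but the t test still works with about 0.0323. It therefore rejects only when the difference exceeds 1.994/√(1 − R²) true standard errors: 1.99, 2.10, 2.23 and 2.38 for R² of 0, 0.1, 0.2 and 0.3. The type I error and t-test power below come from simulation under perfect balance, with the standard error estimated from the data. Reading these thresholds off a normal curve would give slightly low type I errors (4.6% at R² = 0, where the true value is 5%).

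**Step 4: what the adjusted model does.** The residual SD becomes 0.1369 × √(1 − R²), and the noncentrality is 0.09 divided by the reduced standard error. With 68 degrees of freedom (two binary factors assumed), power comes from the noncentral t distribution.

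| R² (assumed) | True SE | Noncentrality | t-test type I error | t-test power | Adjusted power | Unadjusted CI wider by |
|---|---|---|---|---|---|---|
| 0 | 0.0323 | 2.79 | 5.0% | 79% | 79% | 0% |
| 0.1 | 0.0306 | 2.94 | 3.9% | 80% | 83% | 5% |
| 0.2 | 0.0289 | 3.12 | 2.8% | 81% | 87% | 12% |
| 0.3 | 0.0270 | 3.33 | 1.9% | 82% | 91% | 20% |

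The last column is 1/√(1 − R²) − 1.

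**Step 5: does it survive imperfect balance?** Two-factor minimisation was simulated with binary, evenly split factors, a biased coin of 0.8, 72 patients and 6,000 runs per setting. For R² of 0, 0.1, 0.2 and 0.3:

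- t-test type I error was 5.4%, 4.3%, 2.9% and 1.7%;
- t-test power was 79.4%, 80.8%, 81.1% and 81.8%;
- adjusted power was 79.3%, 83.5%, 86.8% and 90.6%;
- adjusted type I error stayed between 5.0% and 5.4%.

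The direction and approximate size agree with the table.

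**The case against.** The strongest reply is that the size rests wholly on an assumed R². The article poses the influence of stenosis on rCBF as an open question, and two design features could keep R² small. Eligible stenosis is limited to 30–70%, and the outcome is already a within-patient ratio to the contralateral side. At R² = 0.1 the loss is about three points of power, and at zero there is none. This stands: the direction is firm, the size is not. It does not defeat the change, because adjusting costs almost nothing when R² is zero (79.3% against 79.4% in the simulation).

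A second reply is that the t test matches the unadjusted sample-size calculation and errs on the safe side. That is true, and it is why this is a matter of efficiency and calibration, not validity.

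A reader might infer more than the article supports:

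- **That the result would be invalid or the false-positive rate inflated.** The error runs the other way; the type I error is at or below 5%.
- **That the t test explains the gap between about 79% and the stated 90% power.** That gap comes from the sample-size calculation and is there at R² = 0. Adjustment closes it only if R² is near 0.3.
- **That adjustment is the only way to gain power without enrolling more.** The outcome is imaged at about 24 hours. If all 40 enrolled per group are imaged, the unadjusted t test has about 83% power, which equals the adjusted gain at R² = 0.1.
- **That the lack of a named interaction test or of further baseline covariates is an error.** The article is condensed, and an analysis plan not shown may supply both.

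**Conclusion.** The point holds as a conditional loss of efficiency. The article balances on two factors and fixes a main test that ignores them. If the factors are prognostic, the interval is too wide and power is lost: about 3, 6 and 9 points at assumed R² of 0.1, 0.2 and 0.3, and none at zero. These figures assume 36 analysed per group, a true difference of 0.09, the pilot SDs, two binary factors and good balance from minimisation. The change is worth making because it can gain power, costs almost nothing if the factors prove unrelated to the outcome, and brings the analysis into line with the allocation.

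**What to change.** In Statistical analysis (2.9), replace the t test for the key primary outcome with a linear model of the 24-hour relative reduction in peri-hematoma rCBF on treatment, level of stenosis and location of stenosis, with the factors coded as in the minimisation. Report the adjusted difference with its 95% confidence interval, and keep the unadjusted t test as a sensitivity analysis.

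The cost is about two degrees of freedom if each factor has two levels. No new patients or data are needed, since both factors are recorded for allocation. Because the t test is stated in the published protocol, the change belongs in a protocol amendment as well as in the analysis plan, and it must be dated before any outcomes by arm are seen.
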